### Outcome measures

#### Feasibility evaluation

The outcome measures for both samples of participants will be mainly based on guidelines from Bowen et al. to assess the feasibility of the REVIVER interventions, including [42]:
*Demand*Outcomes of interest for demand of the interventions include whether the survivors prefer the REVIVER intervention to care as usual, whether the survivors intend to continue applying the content of the interventions in daily life and whether the medical professionals perceive demand for using the REVIVER interventions in daily practice.*Adherence of survivors with interventions (actual use)*Outcome of interest for adherence with the interventions includes the percentage of planned sessions joined by the survivors.*Acceptability*Outcomes of interest include the satisfaction and perceived appropriateness in both survivors and medical professionals with the content and delivery of the REVIVER interventions and fit within the organizational culture.*Practicality*Outcomes of interest include the experiences with the mode of delivery of the REVIVER interventions for both survivors and medical professionals in terms of efficiency, ability to carry out the intervention activities and positive and negative effects on the survivors*Integration/implementation of the REVIVER interventions*Outcomes of interest include success or failure of the REVIVER interventions and perceived facilitators and barriers of success or failure of the REVIVER interventions for both survivors and medical professionals.

#### Potential effectiveness evaluation

##### Health-related quality of life

To evaluate the potential effectiveness of the interventions, HRQOL will be assessed in survivors through the disease-specific EORTC quality of life questionnaire (QLQ-C30) [34]. It includes five domains: a functional scale (physical, role, emotional, cognitive, social), and several symptom scales (fatigue, nausea and vomiting, pain, dyspnoea, insomnia, appetite loss, constipation, diarrhoea, financial difficulties) are incorporated in the QLQ-C30 questionnaire. It concludes with 2 items to assess the survivor’s global health status. All items, with the exception of the global health status items, are scored on a 4-point Likert-type scale with the response alternatives “not at all”, “a little”, “quite a bit” and “very much”. Global health status is scored on a 7-point scale at which the patients can indicate how they perceive their own health status and quality of life with 1 equalling “very poor” to 7 equalling “excellent”. Higher scores on the functional scale and global health status indicate a higher HRQOL. Internal consistency of the QLQ-C30 has shown to be high with a Cronbach alpha of 0.95 and 0.94 for healthy people and patients with cancer, respectively [43, 44].

##### Fatigue

Level of fatigue will be determined in survivors with the generic CIS20R questionnaire [35]. It assesses fatigue with four dimensions, including subjective experience of fatigue and reduction in motivation, activity and concentration. A 7-point Likert scale is used to score the items. Survivors are asked to rate how strongly they agree with each statement. The CIS20R has been shown to be a valid and reliable tool, with Cronbach alpha ranging from 0.84 to 0.95 in the Dutch general population and groups with diverse medical conditions, including cancer survivors [45].

##### Self-efficacy

The GSE Scale gives a rough estimation of the survivor’s self-efficacy level [30]. Survivors will be asked to indicate to what extent the 10 items apply to how they think or act in certain situations. All questionnaire items utilize a 4-point Likert-type scale, ranging from “completely true” to “completely false”. Even though there is no cutoff point indicating a low or high self-efficacy level, the mean score in German cancer patients was set at 30.63 [46]. Therefore, a score lower than 29 is here considered as a low self-efficacy level. Scholz has shown good psychometric properties (Cronbach alpha of 0.85) of the GSE Scale in Dutch subjects, confirming it to be a valid instrument to examine self-efficacy [47].

##### Self-management

We will assess the survivor’s self-management level with the 27-item disease-specific Self-Management Screening (SeMaS) questionnaire [48]. It screens in which way the survivor is capable of self-management in case of chronic diseases and when confronted with difficult situations. At baseline, all 27 items will be included, distributed over the subscale education (1 item), burden of disease/late effects (1 item), control coordination (3 items), own effectiveness (2 items), social support (1 item), coping style (9 items), fear (4 items), depression (3 items) and skills such as computer skills (3 items). At T1 and T2, the education subscale is omitted. Response scales range from a 4-point Likert-type scale (“completely disagree” to “completely agree”) to a 5-point Likert scale (“no” to “very often or all the time”). Items will be scored according to the manual. In addition, a personal profile will be created based on aspects that are important for self-management. Each aspect is divided into three categories: (i) capable of (more) self-management, (ii) capable of self-management with minor barriers and (iii) major barrier(s) for (more) self-management. For the psychometric characteristic coping (problem-solving) and self-efficacy, Cronbach alpha for internal consistency was found to be acceptable (0.70) and good (0.86), respectively [48].

##### Lifestyle

To assess lifestyle changes over time, we will provide the survivors the “Leefstijlvragenlijst” questionnaire. The questionnaire is comprised of a compilation of existing validated questionnaires: the Fragerström Test for Nicotine Dependence, the short version of the International Physical Activity Questionnaire (IPAQ), a questionnaire on eating habits and the Alcohol Use Disorders Identification Tests (AUDIT) [37–40]. In addition, items on the survivor’s motivation level to improve smoking behaviours, physical activity levels, eating habits, alcohol use and weight are also included in the questionnaire [40]. To gain more insight in the physical activity level of the survivors, we will assess physical activity as a lifestyle factor separately with the SQUASH questionnaire. The validated SQUASH questionnaire includes 4 domains on commuting activities, physical activity at work or school, household activities and spare time [41]. Wendel-Vos showed the SQUASH to be a fairly reliable and reasonable questionnaire with a Spearman correlation coefficient for overall reproducibility of 0.58 in Dutch subjects (95% CI 0.36–0.74) [41].

### Analyses

#### Feasibility evaluation

To analyse qualitative data from interviews with survivors and medical professionals, the qualitative data analyses and research software Atlas.ti will be used. The REVIVER study uses grounded theory as methodological orientation to explore the survivors’ and medical professionals’ experiences with the REVIVER interventions. Therefore, an inductive approach to data analyses will be applied. Prior to analyses, the audio-recorded interviews will be fully transcribed verbatim. Subsequently, a first interpretation of the transcription will be made by thoroughly reading the transcript. Next, the transcript will be encoded by two independent coders, after which the codes will be clustered into subthemes. Any disagreements between coders will be discussed until consensus has been reached. If necessary, a third coder will be consulted to reach a consensus. Lastly, the subthemes will be grouped into major themes.

#### Potential effectiveness evaluation

All analyses will be conducted with the statistical software program SPSS (v25). Descriptive analyses will be conducted using mean with standard deviation, median with interquartile range and frequency for baseline characteristics. These variables include gender, age at intervention and treatment, socio-economic status, previous cancer diagnosis and treatment received. The validated questionnaires will be scored and analysed according to the instructions given by the authors of the questionnaires [49]. Potential covariates such as duration and amount of sessions per survivor will be presented as mean and standard deviation as well. To examine differences in the outcome measures over time, a mixed effect model with random intercept and slope will be used. In total, two nurses are assigned to deliver the interventions. The nurse who delivers the interventions may influence the survivor’s outcome. Therefore, nurse is here considered as a random effect. The outcome measures will serve as independent variables in this model with time and potential covariates as dependent variables. Tukey’s HSD test will be used as well to adjust for multiple comparisons. Due to limited power of our study, we will report data with 95% confidence intervals where needed. In addition, all data of our hypothesis testing will be treated as preliminary and with caution. Lastly, we will analyse all data according to the intention-to-treat analyses.

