#### Potential effectiveness evaluation

The REVIVER study was primarily designed for feasibility evaluation of the REVIVER interventions. Our secondary aim is to gain insight into the potential effectiveness of the interventions. We estimate that a total of 60 CAYA cancer survivors with 20 survivors per type of intervention is feasible to reach this aim.

This sample size is realistic considering the number of CAYA survivors invited to the outpatient clinic at the Centre of Expertise for Cancer Survivorship per month (± 48) and the study running time of 24 months. Approximately 1 out of 10 CAYA survivors will be eligible for the interventions and be referred to the REVIVER interventions, resulting in a total of 116 eligible survivors after 24 months. Assuming a recruitment rate of 50%, a sample size of 60 will allow us to gain sufficient insight into potential effectiveness of the REVIVER interventions.

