### REVIVER interventions

The REVIVER interventions are designed for CAYA survivors to receive coaching to cope with direct or indirect late effects of cancer and are delivered by qualified nurses via secured screen-to-screen video calling software. The interventions, elaborating on PCC principles, are aimed at improvement of (i) symptoms of CRF, (ii) self-efficacy and self-management or (iii) lifestyle. The REVIVER interventions consist of an intake, 3 to 6 screen-to-screen video-coaching sessions and a reflection session. On average, the intake session as well as the coaching sessions will be delivered within a 3-month time period. After a 6-month period in which the survivor can actively work on his or her goals set during the coaching sessions, a reflection session will follow. Depending on the type of intervention, the content is based on CBT and/or MI techniques (Table 2). Fidelity of the REVIVER interventions will be pursued in the three following ways:

**Table 2 Tab2:** REVIVER interventions

Goal	To empower, to motivate and to coach CAYA survivors to actively work on improving and managing either CRF, self-efficacy and self-management or lifestyle
Type	Individual eHealth nurse-led video-coaching interventions delivered during screen-to-screen sessions
Duration	An intake session, 3–6 coaching sessions over a time course of approximately 3 months, and a 6-month follow-up reflection session. Average duration of each session is 30–45 min
Basic principle	Person-centred care
Structure	
• Phase 1 (intake) *Engaging with survivor/focus setting*	During the intake, the nurse will reflectively listen to the survivor’s narrative, try to build a mutually trust with the survivor and explore the survivor’s stage of change. Focus for the following sessions will be discussed
• Phase 2 (3–6 sessions) *Coaching with evidence-based modules of CBT and/or MI*	According to needs and preferences of the survivor, 3–6 coaching sessions will follow Content of the interventions: o *CRF*: module of cognitive behaviour therapy light for chronic fatigue after cancer [31] o *Empowerment*: module cognitive behaviour therapy on four-phase recovery for cancer survivors and motivational interviewing for goal setting [32] o *Lifestyle*: motivational interviewing according to the stage of change of survivor [33]

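### The stated model names no intervention-type-by-time term, so the time effect on each target-specific secondary outcome is averaged over a sample in which 40 of 60 were referred for a different target

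*Protocol article*

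**What the plan says.** The Sample size section of the protocol article plans "a total of 60 CAYA cancer survivors with 20 survivors per type of intervention". The REVIVER interventions section describes the three types as "aimed at improvement of (i) symptoms of CRF, (ii) self-efficacy and self-management or (iii) lifestyle". Table 1 gives each type its own referral indication: fatigue criteria, low empowerment, or unhealthy lifestyle factors. Table 2 gives each its own content: a CBT module for fatigue, CBT plus motivational interviewing for empowerment, and motivational interviewing for lifestyle. Under Study population, a survivor is eligible if referred to one of them.

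The Design section treats the quantitative part as a single arm measured at T0, T1 and T2. The Analyses section (Potential effectiveness evaluation) then gives one model: "To examine differences in the outcome measures over time, a mixed effect model with random intercept and slope will be used". Its explanatory terms are time and potential covariates, with nurse as a random effect. I read the outcome as the response, although the text swaps the labels dependent and independent. The only covariate examples are introduced by "Potential covariates such as duration and amount of sessions per survivor". Intervention type is not mentioned there as a fixed effect, an interaction, a stratum or a baseline variable.

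Health-related quality of life is the primary effectiveness outcome (Abstract). Fatigue, self-efficacy, self-management and lifestyle are secondary, and all survivors complete all questionnaires (Table 3).

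**The concern.** The sample is set by intervention type, but the model as written has nothing that lets change over time differ by type. Its time effect on the fatigue score, for example, averages survivors coached on fatigue with survivors coached on empowerment or lifestyle. The same holds for the self-efficacy, self-management and lifestyle outcomes.

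The groups are also selected differently. A high fatigue score is a route into the fatigue intervention only, and a low self-efficacy score a route into the empowerment intervention only. Room to improve on a given outcome, and regression to the mean in a study without controls, can therefore differ by type.

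At stake is the secondary objective, which is insight into potential effectiveness on exactly these outcomes. A module that works on its target could look weak because two other groups dilute it. A strong change in one group could equally be read as a property of all three. The article gives nurse a term because the nurse may affect outcome. The type of coaching is at least as likely to do so.

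**Working it through.** **1. The plan's own figure.** The inputs, from the Sample size section, are about 48 invited survivors "per month (± 48) and the study running time of 24 months", 1 in 10 eligible and referred, and 50% recruited.
- Eligible: 48 × 24 × 0.10 = 115.2 (stated: 116).
- Recruited: 116 × 0.50 = 58 (stated: 60).
- Split: 3 × 20 = 60.

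The 60 reproduces to within rounding. It is a recruitment figure. The article states no effect size, SD or power.

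**2. Share referred for a different target.** For any one target this is (60 − 20)/60 = 40/60 = 66.7%.

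**3. What the averaged time effect estimates.** Let d be the on-target change in units of the within-type SD of change, and f the off-target change as a fraction of d. Both are assumptions. With equal groups:

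pooled change = (d + 2fd)/3 = d(1 + 2f)/3

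This is d/3 at f = 0, 2d/3 at f = 0.5, and d at f = 1.

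**4. Power.** I used a two-sided 5% paired t test (noncentral t), complete data and equal SDs. The pooled variance of change includes the spread between types:

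variance = 1 + [(d − pooled)² + 2(fd − pooled)²]/3

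Example, d = 0.5 and f = 0: pooled = 0.5/3 = 0.167, variance = 1 + 0.25 × 2/9 = 1.056, power 23.5%.

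| d | f | Pooled change (SD) | Power, pooled n = 60 | Power, target group n = 20 |
|---|---|---|---|---|
| 0.3 | 0 | 0.10 | 11.7% | 24.7% |
| 0.3 | 0.25 | 0.15 | 20.6% | 24.7% |
| 0.3 | 0.5 | 0.20 | 33.0% | 24.7% |
| 0.3 | 1 | 0.30 | 62.8% | 24.7% |
| 0.5 | 0 | 0.17 | 23.5% | 56.5% |
| 0.5 | 0.25 | 0.25 | 46.7% | 56.5% |
| 0.5 | 0.5 | 0.33 | 71.3% | 56.5% |
| 0.5 | 1 | 0.50 | 96.8% | 56.5% |
| 0.8 | 0 | 0.27 | 47.7% | 92.4% |
| 0.8 | 0.25 | 0.40 | 83.5% | 92.4% |
| 0.8 | 0.5 | 0.53 | 97.9% | 92.4% |
| 0.8 | 1 | 0.80 | about 100% | 92.4% |

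At d = 0.5 the two powers are equal (57%) when f is about 0.35. Below that the target group alone has more power; above it the pooled sample does.

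**5. Precision.** The 95% CI half-width, in SD of change, is t(0.975, n − 1)/√n. It is 0.47 for n = 20 and 0.26 for n = 60.

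**6. A main effect is not enough.** Type entered only as a covariate shifts each group's level, but still leaves one time effect averaged over the three groups. A type-by-time term or per-type estimates are needed.

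**The case against.** **Pooling is inferred.** The article never says the groups are pooled. Its covariate list is open, the target of 20 per type is compatible with by-type reporting, and a fuller analysis plan may exist. A reader might infer that the authors have decided against by-type estimates, and the text does not support that. What stands is narrower. The article sets out the model in some detail (random terms, nurse, covariates, multiplicity test), and with the single-arm label one averaged time effect is its natural reading.

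**The primary effectiveness outcome is largely untouched.** All three types are expected to improve quality of life, so a pooled estimate is defensible there. This stands in full and limits the point to secondary outcomes of a secondary objective.

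**Spillover is plausible.** Table 2 gives all three types a shared goal of empowering and coaching, on a person-centred basis. The Background says person-centred care promotes self-efficacy and self-management. Zero off-target change is therefore an extreme assumption, above all for those two outcomes. This also stands: the power argument reverses above about one third spillover.

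**Two further inferences are not supported.** A reader might say the plan fails to show which intervention should go to a randomised trial. The article speaks of the interventions collectively and never promises to select one, and 20 uncontrolled survivors per type would not settle it. A reader might also object to session number and duration as covariates. That is a separate and debatable matter. The article does not call them confounder adjustments, and it already plans to summarise them descriptively.

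**Conclusion.** The point holds in a limited form. The sample is planned by intervention type, but the stated model has no type-by-time term. Followed as written, its time effect on fatigue, self-efficacy, self-management or lifestyle mixes 20 survivors referred for that target with 40 who were not. Unless all three groups change equally, the result does not estimate the effect of any one intervention. That conclusion needs no assumed effect size.

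The size of the distortion does need one. The averaged effect lies between one third of the on-target change (no spillover) and all of it (full spillover). A reader might take threefold dilution and a loss of power as the general result. They are only the zero-spillover end of the range, and with half spillover averaging gains power. The reason to change the plan is what is being estimated, not power.

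The change is worth making but is not critical. Feasibility is the primary objective, and the article already treats its hypothesis tests as preliminary.

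**What to change.** In the Analyses section, add intervention type and type-by-time as fixed effects, with time as a three-level factor. Report the T1−T0 and T2−T0 changes with 95% CIs within each intervention for its matching outcome:
- CIS20R for the fatigue intervention
- General Self-Efficacy Scale and SeMaS for the empowerment intervention
- lifestyle questionnaire and SQUASH for the lifestyle intervention

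Label these estimates descriptive and preliminary. Without controls, they also carry any regression to the mean from selecting survivors on the same problem. Quality of life may stay pooled, with by-type estimates alongside.

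The change is to wording only, because type is known from referral. It adds 2 + (2 × 2) = 6 fixed-effect parameters. By-type intervals are wider, about ±0.47 SD of change at n = 20 against ±0.26 SD pooled at n = 60, and wider still if survivors drop out.

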## Discussion

Health-related quality of life can be seriously affected in CAYA cancer survivors coping with late effects of their cancer treatments. This illustrates the necessity of high-quality and multidisciplinary cancer survivorship care to either prevent or treat late effects or to preserve the survivor’s health. We believe, inherent to the PCC principles applied at our cancer survivorship care clinic, that a survivor should no longer be seen as a patient to which care is prescribed by a doctor but as an individual taking control of their own health and health behaviours. In that line of thought, continuing life as normally as possible is rather essential for survivors. However, for some survivors, interventions are necessary to cope with late effects. Therefore, screen-to-screen eHealth interventions designed according to the survivors’ own preferences to relief them from unnecessary clinic visits seem promising. Our study is motivated by the potential value of eHealth interventions for this relatively young population. In addition, we believe that PCC, as the core principle of the REVIVER interventions, as well as the evidence-based content of all three types of interventions (CBT and/or MI), will be important contributing factors in improving the participant’s quality of life.

The decision to design interventions for CRF, self-efficacy and self-management and lifestyle is primarily based on the doctors’ and nurses’ experiences from the outpatient clinic. In addition, literature has stated the severity of CRF as a late effect of treatment, whereas maintaining or adopting a healthy lifestyle is crucial to prevent development of late effects [9–18]. On the other hand, a low self-efficacy status, due to a history of cancer, can have a negative impact on the survivor’s psychosocial domain. Likewise, when navigating through the healthcare system, low self-efficacy or self-management can be a real obstacle for the survivor. With regard to the outpatient clinic visit at the Centre of Expertise for Cancer Survivorship, survivors benefit the most of PCC when their self-efficacy level is sufficient. Therefore, we believe that targeting these specific survivorship difficulties will yield the most benefits.

The mixed methods design to evaluate the REVIVER interventions, including qualitative interviews and quantitative questionnaires, will enable us to gain a broad and in-depth insight in the feasibility and potential effectiveness of these interventions. Most importantly, we will be able to identify areas for improvement. This is paramount for further implementation of the interventions and designing a randomized controlled trial to assess (cost-)effectiveness of the REVIVER interventions on a larger scale.

However, the REVIVER study has some limitations. A first note of caution is due to the fact that we lack a control group for comparisons. Given that the interventions are implemented as care as usual at our cancer survivorship clinic, we believe it is not ethical to withhold survivors from receiving this care. Therefore, for our study, we did not opt for a control group. Instead, we will apply a pre-post design with three measurement points to gain insight in the potential effectiveness of the REVIVER interventions. Another limitation is inherent to the small nature of this feasibility study, which impedes us in providing robust data on potential effectiveness of the interventions. Notwithstanding these limitations, this study will offer us important insights into the feasibility of the REVIVER interventions.

In conclusion, given the content of the REVIVER interventions with PCC as core principle, as well as the mode of delivery, the REVIVER interventions may be a feasible and potential effective tool in delivering interventions as part of cancer survivorship care to treat or prevent late effects of cancer.

